## Abstract

**Background:**

Sleep is an essential component of good physical and mental health. Previous studies have reported that poor quality sleep is associated with an increased risk of hypertension and cardiovascular disease. Hypertension is the most common and important risk factor for cardiovascular disease, and even modest reductions in blood pressure can result in significant reductions in the risk of stroke and myocardial infarction. In this trial, we will determine the efficacy of an online sleep intervention in improving blood pressure, in participants with hypertension and poor sleep quality.

**Methods:**

*Trial design:* Randomized-controlled, two-group, parallel, blinded, single-center, Phase II trial of 134 participants. *Population and recruitment*: Primary prevention population of participants with hypertension (systolic blood pressure, 130 to 160 mm Hg; diastolic blood pressure, <110 mm Hg) and poor sleep quality in a community setting. *Intervention:* Multicomponent online sleep intervention consisting of sleep information, sleep hygiene education, and cognitive behavioral therapy. *Comparator:* Standardized cardiovascular risk factor and lifestyle-education session (usual care). *Primary outcome:* Change in mean 24-hour ambulatory systolic blood pressure between baseline and 8-week follow-up. Hypertension has been selected as the primary outcome measure because of its robust association with both poor sleep quality and cardiovascular disease. *Statistical analyses*: Intention-to-treat analysis by using a linear mixed model.

**Trial registration:**

ClinicalTrials.gov: NCT01809821, registered March 8, 2013.

## Background

### Insufficient or poor quality sleep and cardiovascular risk

Sleep is an essential component of good physical and mental health. However, the average sleep duration in the Western world has steadily declined over the past decade
[1]. In the National Health Interview Survey 2004 to 2007, more than one third of the North American adult population was noted to have an abnormal duration of sleep, defined as too short (<7 to 8 hours per night) or too long (>8 hours per night)
[2]. Previous laboratory and epidemiologic studies showed that inadequate sleep patterns, in terms of both quality and quantity, are associated with an increased frequency of cardiovascular risk factors such as hypertension, diabetes mellitus, and obesity
[3, 4], as well as independently associated with an increased risk of adverse cardiovascular outcomes, such as stroke and myocardial infarction
[5, 6]. A meta-analysis of 16 prospective cohort studies reported a significant association between sleep of short duration (≤5 to 6 hours per night) and long duration (>8 to 9 hours per night) and an increased risk of all cause-mortality
[7]. Therefore, insufficient or poor-quality sleep is a common risk factor for cardiovascular disease (CVD) and all-cause mortality, and represents a potentially important population-based modifiable target for CVD prevention.

### Inadequate sleep and hypertension

A number of epidemiologic studies have reported an association between inadequate sleep, in terms of duration and quality, and an increased risk of hypertension
[1, 8–10]. A cross-sectional study among healthy adolescents reported an association between actigraphy-defined low sleep efficiency (an objective measure of sleep quality, defined as the percentage of time in bed estimated to be asleep) and prehypertension, after adjusting for known confounding factors (OR, 3.5; 95% CI, 1.5 to 8.0)
[11].

Furthermore, in a substudy of 578 adults from the Coronary Artery Risk Development in Young Adults study, actigraphy-measured shorter sleep duration and lower sleep maintenance (a component of sleep quality defined as the percentage of time between initial sleep onset and final waking that is spent sleeping), were noted in a cross-sectional analysis to be associated with significantly higher systolic and diastolic blood pressures, after adjusting for confounders such as age and antihypertensive medications. In a longitudinal analysis of this cohort, shorter average sleep duration also predicted significantly increased odds of incident hypertension over 5 years (OR, 1.37; 95% CI, 1.05 to 1.78)
[12]. In addition, a longitudinal analysis of data from the National Health and Nutrition Examination Survey of >4,500 US adults, reported a significantly increased risk of hypertension in individuals sleeping ≤5 hours per night compared with those sleeping for 7 to 8 hours per night, after adjusting for various potential confounders (HR, 1.32; 95% CI, 1.02 to 1.71)
[1].

### Mechanism underlying the association between poor sleep and hypertension

The mechanism underlying the association between insufficient or poor-quality sleep and hypertension is proposed to be multifactorial, including increased sympathetic nervous system activity and increased prevalence of intermediate risk factors, such as poor diet, reduced physical activity, increased weight, and smoking
[13]. Laboratory studies have noted significantly increased sympathetic activity and blood pressure in individuals in a sleep-restricted condition, compared with individuals in a sleep-recovery condition
[14–17]. Increased urinary excretion of noradrenaline, indicating increased sympathetic activity, has also been reported after a night of sleep deprivation
[15, 17]. Increased activity of the sympathetic nervous system can lead to vasoconstriction as well as fluid retention, which can lead to hypertension through volume overload
[18].

Blood pressure and heart rate typically exhibit diurnal variation. During sleep, a nocturnal dip occurs in both blood pressure and heart rate, which remain low until the time of awakening. Reduced sleep duration can result in longer exposure to enhanced sympathetic activity and increased average 24-hour blood pressure and heart rate. In this way, habitual sleep restriction can lead to prolonged enhanced sympathetic nervous system activity, the development of hypertension, and subsequently, an increased risk of stroke and other CVD
[1].

### Poor sleep and other cardiovascular risk factors

The mechanism underlying the association between poor sleep and other key risk factors for CVD, such as diabetes mellitus and obesity, is thought to be due to sleep-related disruption in metabolic, endocrine, and immune functions. Insufficient sleep has been associated with elevated evening cortisol concentrations, which can result in reduced sensitivity to insulin; increased levels of growth hormone, which can cause a transient insulin resistance; and increased sympathetic nervous system activity, which can inhibit insulin secretion from the pancreas
[13, 14, 19]. Thus, sleep-induced disruption of the endocrine and autonomic systems could explain the observed association between inadequate sleep and increased occurrence of diabetes mellitus.

Curtailed sleep has also been associated with reduced levels of leptin, a hormone released by adipocytes, which promotes satiety, and increased levels of ghrelin, a hormone secreted by the stomach and pancreas that stimulates appetite, as well as an increase in subjective feelings of hunger. Thus, this provides a possible mechanism for the observed association between inadequate sleep and obesity
[20, 21]. Increased activity of the sympathetic nervous system, with resultant hypertension, is thought to be the underlying pathophysiologic mechanism linking insufficient sleep with diabetes, obesity, and CVD
[18]. In turn, these factors also contribute to an increase in blood pressure.

### Current educational interventions to modify traditional cardiovascular risk factors

Currently, stroke and other CVDs are the leading causes of mortality in Europe and North America. Existing interventions to tackle the huge burden of CVD in the population include education on lifestyle modification, as well as the use of primary and secondary preventive therapies
[22]. Educational interventions typically consist of advice and information on modifiable risk factors, such as smoking, alcohol consumption, physical activity, and dietary practices. Although factors such as poor diet and lack of physical activity clearly play a central role, another possible contributor to the current epidemic of CVD, mediated through hypertension and the metabolic syndrome, is insufficient or poor-quality sleep
[13].

### Modifiability of poor sleep and the potential role of a sleep intervention in CVD prevention

Insufficient or poor sleep quality is a modifiable risk factor for CVD and could potentially be improved through the use of a simple, low-cost, multicomponent intervention aimed at improving sleep quality and quantity. Three previous randomized controlled trials investigating the efficacy of an intervention to improve sleep in participants with insomnia reported significant improvements in sleep efficiency, sleep latency and wakefulness after sleep onset (measures of sleep quality), as well as improvements in mental health and energy
[23–25]. Improving sleep quality has been suggested as a therapeutic target for the modification and prevention of cardiovascular risk factors, such as hypertension
[1, 12, 26]. Despite its apparent importance, no previous randomized controlled trials have investigated the efficacy of a sleep intervention for lowering blood pressure or reducing the risk of CVD.

In this randomized controlled trial, we evaluate the efficacy of a sleep intervention in controlling blood pressure and other vascular risk factors in a primary prevention population of individuals with hypertension and poor sleep quality.

### Primary aim

To determine whether the addition of a multicomponent, online, sleep intervention to usual care (standard cardiovascular risk factor education), results in a greater reduction in mean 24-hour systolic blood pressure (SBP) in participants with hypertension and poor sleep quality, compared with usual care alone, over an 8-week period.

### Secondary aims

To determine whether the addition of a multicomponent, online, sleep intervention to usual care results in a greater reduction in mean 24-hour diastolic blood pressure (DBP) in participants with hypertension and poor sleep quality, compared with usual care alone, over an 8-week period.To determine whether the addition of a multicomponent, online, sleep intervention to usual care results in greater improvements in body mass index (BMI), plasma lipids, plasma HbA1c, estimated glomerular filtration rate (eGFR), mean number of cigarettes smoked per day, Sleep Condition Indicator (SCI) Score, Insomnia Severity Index (ISI) score, Pittsburgh Sleep Quality Index (PSQI) score, sleep-onset latency (SOL), wake time to sleep onset (WASO), sleep efficiency, total sleep time (TST), Beck Depression Inventory (BDI) score and Beck Anxiety Inventory (BAI) score, in participants with hypertension and poor sleep quality, compared with usual care alone, over an 8-week period.To determine whether level of adherence to the sleep intervention influences the change in mean 24-hour SBP over an 8–week period.To determine whether concomitant use of antihypertensive medication influences the change in mean 24-hour SBP over an 8–week period.

## Methods

### Trial design

Randomized, two-group, parallel, blinded, controlled, single-center trial. This is a Phase II, efficacy, proof-of-principle trial with an allocation ratio of 1:1.

### Setting: Identification of participants and description of center

Participants are recruited via advertisements in local newspapers, advertisements on local radio stations, local and online (Twitter and Facebook) poster advertisements, and local public screening events. Interested participants with hypertension (average SBP readings between 130 and 160 mm Hg with average DBP <110 mm Hg) are referred to the Health Research Board Clinical Research Facility Galway (HRB-CRFG) to be screened for trial eligibility. Those who meet the eligibility criteria are then referred to Croí House, Galway City, for baseline risk factor assessment and for provision of written informed consent. Croí House is an established cardiovascular risk factor modification center that provides medical assessment, risk-factor profiling, and educational sessions on cardiovascular risk-factor modification to the local population. Eligible participants are randomized into two management groups: (a) usual care + online sleep intervention, and (b) usual care.

### Choice of study population

Our study is a Phase II trial. A primary prevention population of participants with no previous CVD and poor sleep quality has been chosen because of the high likelihood of such participants being responsive to the intervention and demonstrating a reduction in blood pressure with the intervention. Potential participants already receiving antihypertensive medications are eligible for inclusion in the trial. However, participants with diabetes mellitus and chronic renal impairment are excluded, which should reduce the proportion of participants that will have changes to their blood-pressure medications over the course of the trial.

### Eligibility criteria

#### Inclusion criteria

Signed written informed consent≥ 18 years on entry to studyAverage automated SBP monitor readings between 130 and 160 mm Hg with average automated DBP monitor readings <110 mm Hg on three occasions, measured in a valid standardized manner while seated; or average 24-hour ambulatory blood pressure monitoring (ABPM) SBP readings between 130 to 160 mm Hg with average DBP readings <110 mm Hg.Self-reported difficulty getting to sleep (defined as usually taking more than 30 minutes to get to sleep), and/or staying asleep (usually waking up more than once per night) for at least 3 months’ durationInternet access, self-reported competency in using the Internet, and regular Internet use

#### Exclusion criteria

Currently receiving more than two antihypertensive medications, or recent (within previous 8 weeks) change in type or dose of antihypertensive medications or planned change in antihypertensive medication in next 8 weeks.History of myocardial infarction, ischemic stroke, or transient ischemic attackHistory of congestive heart failureHistory of dialysis or evidence of chronic kidney disease (eGFR <60)History of diabetes mellitusCurrent ongoing sleep-hygiene education or sleep-related cognitive behavioral therapyOngoing involvement in night-shift workHistory of obstructive sleep apnea (OSA) and previously received or currently receiving treatment for OSA (participants with a history of untreated OSA are eligible for inclusion).Known history of sleep disorders (that is, narcolepsy; hypersomnias; parasomnias such as sleep walking, night terrors, recurring nightmares; periodic limb movements/restless-leg syndrome; circadian rhythm sleep disorder)Unable to follow educational advice in the opinion of the clinicianBaby or young children at home that wake during the nightHistory of bipolar affective disorderHistory of psychosisHistory of major depression (defined as depression requiring hospitalization in the past or visit to psychiatry outpatient clinic in the past 3 months)Unstable depression (unstable is defined as changes in antidepressant medications within the last 3 months (that is, starting a new medication, stopping a medication, or changing a medication dose).Unstable anxiety disorders/panic attacks (unstable is defined as changes in anxiolytic medications within the last 3 months (that is, starting a new medication, stopping a medication, or changing a medication dose).Ongoing substance or alcohol abusePlanned surgery or hospitalization during the trialIncapacitating pain or illness or other medical condition in which, in the opinion of the clinician, the sleep intervention is unlikely to be effective.

Participants who are currently taking medications associated with sleep disturbances are not excluded from this study, provided they have been stable on those medications for >3 months (stable is no start, stop, or change in dose in past 3 months). These medications include:

antidepressants (selective serotonin reuptake inhibitors, venlafaxine, duloxetine, monoamine oxidase inhibitors)antipsychoticsamphetamine derivativesdecongestants (pseudoephedrine, phenylephrine, phenyl propanolamine)narcotic analgesics (oxycodone, codeine, propoxyphene)cardiac medications such as β-blockers, α-receptor agonists and antagonists, diuretics, and lipid-lowering agentspulmonary medications (theophylline and albuterol)

### Randomization

A randomization strategy using randomly permuted blocks of varying block size is being used, which allows the assignment schedule to be preplanned before participant recruitment. The randomization schedule is constructed by using a computer-generated list of pseudo-random numbers. A centrally administered, computer-generated randomization scheme is being used to assign individual participants randomly in a 1:1 ratio, to either the intervention or control groups. Once a participant is deemed eligible for trial entry and has provided written informed consent, a researcher assigns a unique study-identification number to the participant and contacts the online sleep intervention (Sleepio) team with the participant's name, their assigned participant number, and contact details (Email address and telephone number). The Sleepio team then assigns the participant to the next available randomization number on the list, corresponding to a particular treatment assignment (Sleepio intervention or control). Participants randomized to Sleepio receive a code via Email to access the online sleep intervention. The Sleepio team holds the central record of all participants who have been randomized, along with the corresponding randomization numbers and treatment-group assignments. All investigators at the HRB-CRFG, including the statistician, are blinded to participant treatment-group assignment. At the end of the trial, treatment assignments will be compared with the randomization list, to detect any incorrect assignments, and following completion of statistical analyses, all investigators and trial personnel will be unblinded.

### Blinding

Trial participants, investigators, data collectors, statistician, and outcome assessors are blinded to study-group assignment. Members of the Sleepio team assigning participants to treatment groups are not blinded. Participant consent forms and information leaflets state that a behavioral lifestyle intervention is being compared with a control, and describe the intervention as general education on cardiovascular risk factors. It is also mentioned that aspects of the intervention are delivered via online web sessions, as well as through face-to-face sessions. Cardiology research nurses deliver the usual care intervention (that is, the cardiovascular education intervention) to participants in both treatment arms.

All laboratory measurements are carried out in a blinded fashion. Laboratory samples, with the exception of HbA1c serum levels, are frozen and then stored, and will be analyzed at the end of the trial. Serum HbA1c levels are measured on the day of collection. Blood pressure measurements are recorded in a blinded fashion by using a 24-hour automated blood pressure monitor, thus avoiding observer bias. All other study measurements, including BMI and questionnaire scores, are interpreted and entered into the study database in a blinded fashion by a trained researcher. Because of the nature of the intervention, a requirement for breaking the blinding to access the randomization schedule for a particular participant during the trial is not anticipated.

### Study interventions

#### Components of the sleep intervention

The sleep intervention (Sleepio) is a multicomponent online intervention consisting of sleep information and sleep-hygiene education, along with behavioral and cognitive components. This intervention was developed after consultation with a sleep psychologist. It is based on three previous randomized controlled trials investigating the efficacy of an intervention to improve sleep in participants with insomnia, one of which was an online cognitive behavioral therapy intervention for chronic insomnia disorder
[25]. The interventions were similar, with two of the trials showing a significant improvement in sleep efficiency
[23, 25], and the third showing a significant improvement in sleep latency, wakefulness after sleep onset, and sleep efficiency (measures of sleep quality), as well as improvements in mental health and energy
[24].

Participants in the sleep-intervention arm also receive ”usual” care (standardized cardiovascular risk-factor education program), similar to participants in the control arm. Thus, the comparison is: standardized cardiovascular education + online sleep intervention versus standardized cardiovascular education.

### Multicomponent online sleep intervention

#### Sleep information and sleep-hygiene education

The participant is educated on the need for sleep and its functions, the effects of sleep loss, factors adversely affecting sleep, and the impact of lifestyle habits and environmental factors on sleep. Participants are educated on a series of practical steps to improve sleep hygiene:

Avoid caffeinated beverages, nicotine, or other stimulants 6 hours before bedtime.Avoid alcohol, excessive fluids, and large meals, 3 hours before planned bedtime. Eliminate ”nightcaps”.Avoid excessive alcohol intake (14 units for females, 21 units for males, recommend no more than 2 drinks per day)Avoid illicit drugsEngage in regular physical activity, early in the day.Avoid stress and excitement, such as vigorous exercise, in the 2 hours before bedtimeAvoid intense mental activity requiring a high level of concentration, including computer work, in the 2 hours before planned bedtime.Avoid mental activities such as planning or thinking while in bed.Maintain an appropriate sleeping environment, in terms of light, noise, ambient temperature, and comfortable mattress/blankets.Stimulus control: limit the use of the bedroom to sleeping, with avoidance of nonsleep behaviors such as watching television or reading in the sleep environment. Remove incompatible activities from the bedroom environment (for example, television, books). The aim is to break associations between the sleeping environment and being awake, to re-associate the bedroom with sleep, and to stay in the bedroom only when asleep or feeling sleepy.

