#### Sleep scheduling and sleep restriction

To help participants to reshape sleep patterns to correspond with their individual sleep needs. The participant is helped to reestablish a consistent sleep-wake schedule.

Define individual sleep requirements.Develop a good pre-sleep routineEstablish a strong bed-sleep connectionEliminate wakefulness from bed (rising if not asleep within around 20 to 30 minutes)Establish and follow a regular and consistent night-to-night sleep schedule, go to sleep in the same bed at the same time each night, and arise immediately on awakening at the same time each morningIncrease sleep efficiency through scheduling sleep in relation to current total sleep; restrict participants’ allowed time in bed to the actual sleeping time according to the participants’ sleep diary. Adjust the time-in-bed period as sleep efficiency improves from week to week. Participants are instructed to get up at a regular time, even if they did not have enough sleep the night beforeAvoid daytime napsAvoid recovery sleep as compensationEncourage and support people in changing their sleep routines to improve 7-day per week compliance

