## Discussion

### Methods of minimizing bias

One potential limitation of this study is the risk of contamination, if participants or clinicians become aware of individual treatment-group assignments. This could result in the differential use of co-interventions between the two study groups, or use of a sleep intervention in the control group, resulting in bias toward the null. The screening questionnaire for sleep quality is another potential source of unblinding. To minimize the risk of unblinding, it is being administered as a routine baseline screen, along with questionnaires to measure depression, anxiety, and cognitive function.

A second potential limitation is volunteer bias. Individuals who participate in studies are often more healthy than those who refuse to provide consent. Thus, the actual sample of individuals included in the trial may not be representative of the relevant population, limiting the generalizability of the results. Furthermore, study volunteers are often well-motivated, highly adherent individuals who are likely to benefit from such an intervention. This would also affect the external validity of the results. However, this is a proof-of-concept, phase II study, and such a population will maximize the chances of detecting the true treatment effect, before testing the effectiveness of this intervention in a wider population.

A third potential limitation in this study is the primary outcome measure of reduction in mean 24-hour systolic blood pressure, which is a surrogate outcome measure. As this is a pilot study, a clinical outcome would not be feasible, as a relatively long follow-up period would be required to demonstrate a treatment effect. Reduction in blood pressure has been shown to be predictive of significant reductions in major vascular events. Thus, we believe that reduction of systolic blood pressure is an appropriate outcome measure for this study.

A fourth potential limitation of this study is the risk of nonadherence to the intervention, which is a particular challenge in trials evaluating behavioral interventions. However, a number of measures are being implemented to maximize adherence (see earlier). To determine the influence of adherence on the estimated treatment effect, a sensitivity analysis will be performed.

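### Nothing prevents two members of one household from being randomized to different arms, although parts of the sleep intervention act on a shared bedroom and bedtime; the effect is probably small and the remedy cheap

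*Protocol article*

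**What the plan says.** - **Allocation.** The Randomization section describes a scheme "to assign individual participants randomly in a 1:1 ratio", in permuted blocks of varying size. It names no household unit or stratum.
- **Eligibility.** The inclusion and exclusion lists are detailed. The only item about the home concerns young children who disturb the night. The exclusion for sleep education or therapy covers the applicant's own current treatment, not exposure through someone else in the trial.
- **Recruitment.** Under Setting, participants come from local newspapers and radio, and from "local and online (Twitter and Facebook) poster advertisements, and local public screening events".
- **Intervention.** The sleep-hygiene section asks participants to control light, noise and temperature and to "Remove incompatible activities from the bedroom environment (for example, television, books"). The sleep-scheduling section asks them to "go to sleep in the same bed at the same time each night" and to rise at a fixed time.
- **Masking.** The Blinding section states: "Trial participants, investigators, data collectors, statistician, and outcome assessors are blinded to study-group assignment". For participants this works by describing the intervention in general cardiovascular terms, while mentioning that some of it is delivered online.
- **Contamination.** Methods of minimizing bias names "use of a sleep intervention in the control group, resulting in bias toward the null" as a limitation. The one safeguard stated there is to present the sleep questionnaire as part of a routine baseline screen.

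**The concern.** Staff who follow the plan as written could enrol both members of a couple and see them allocated to different arms. The control partner would then sleep in the altered bedroom and live alongside the new schedule. That partner could also see online sleep sessions, a daily sleep diary and reminder messages. Since participants are told that some of the intervention comes through the web, the control partner could work out both allocations and what is being tested.

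Two things are at stake. Exposure of controls shrinks the between-arm contrast. Loss of masking matters most for the sleep, depression and anxiety scores, which are questionnaire-based, and less for the primary outcome, which an automated monitor records. The protocol recognizes this kind of contamination in general terms, but its safeguard does not reach a shared bedroom.

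**Working it through.** **Inputs from the sample-size section and the statistical analysis plan section of the article:** SDs of SBP reduction 8.3 and 7.7 mm Hg; two-sided α = 0.05; 80% power at 4 mm Hg (90% at 5 mm Hg); 5% loss to follow-up; 67 per group.

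**Step 1. Reproduce the plan's figure.** Pooled SD = √[(8.3² + 7.7²)/2] = 8.006. n = 2 × (1.960 + 0.842)² × 8.006² / 4² = 62.9, so 63 per group. Inflated for loss: 63/0.95 = 66.3, so 67. The stated figure reproduces. (An exact t calculation gives 64, then 68, which is close enough.) No figure in the plan is disputed here.

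**Step 2. Power without pairs.** Analysed per arm: 67 × 0.95 = 63.65, about 64. The standard error of the difference is 8.006 × √(2/64) = 1.415. Power at 4 mm Hg = Φ(4/1.415 − 1.960) = 80.7%; at 5 mm Hg it is 94.2%.

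**Step 3. Dilution.** Let f be the share of participants in same-household pairs and t the fraction of the treatment effect passed to an exposed control. The chance that a partner is in the other arm is 67/133 = 0.504. The expected contrast is δ × (1 − f × 0.504 × t). The article gives neither f nor t, so both are assumptions.

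| f (assumed) | t (assumed) | Exposed controls | Contrast from 4 mm Hg | Power | Contrast from 5 mm Hg | Power |
|---|---|---|---|---|---|---|
| 0 | – | 0% | 4.00 | 80.7% | 5.00 | 94.2% |
| 5% | 0.5 | 2.5% | 3.95 | 79.7% | 4.94 | 93.7% |
| 5% | 1.0 | 2.5% | 3.90 | 78.7% | 4.87 | 93.1% |
| 10% | 0.5 | 5.0% | 3.90 | 78.7% | 4.87 | 93.1% |
| 10% | 1.0 | 5.0% | 3.80 | 76.6% | 4.75 | 91.9% |

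Keeping 80% power at 4 mm Hg would take 69-71 per group at f = 5% and 71-74 at f = 10%, against the planned 67.

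**Step 4. Effect of blocking.** Partners who enter one after the other are more likely to be split. Within a block of 4 the chance is 2/3. Block sizes are not stated, so this is illustrative. At f = 10% and t = 1 it gives 4 × (1 − 0.10 × 2/3) = 3.73 mm Hg and power of 75.1%. This needs every pair to share a block of 4 and full transfer, so it is an extreme case.

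**Step 5. Correlation within couples.** In the variance of a difference in means with n per arm, a pair in the same arm adds 2ρσ²/n² and a split pair subtracts 2ρσ²/n². When half of pairs are split the terms cancel. When more than half are split, and ρ is positive, treating partners as independent is if anything conservative.

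**The case against.** The strongest reply is that the problem is hypothetical. The article nowhere says that couples enrol. Both partners would have to meet the same blood-pressure, sleep and medical criteria and volunteer within a sample of 134. This stands: the share of pairs is unknown and may be close to zero.

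A reader might infer that a control partner is in effect treated. The document does not support that. Access is by a personal code, time in bed is set from the participant's own diary, and the cognitive sessions are individually tailored. Only the environmental and scheduling parts pass across, so full transfer is an upper bound.

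A reader might also infer that correlated outcomes within couples invalidate the analysis. The cancellation shown in the working rules that out as a stated harm.

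It can also be said that the protocol already discloses contamination and its direction, and that automated ambulatory monitoring protects the primary outcome from observer bias. Both are true. But disclosure does not close the route, and the monitor does not protect the questionnaire outcomes or prevent real exposure.

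Finally, an article condenses a protocol, and a household rule might stand in the full document. If it does, the point lapses. However, the article prints long eligibility lists and addresses the home in one item, so on this text the gap is in the criteria as written.

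**Conclusion.** The point holds as a cheap design improvement, not as an error in a stated figure. The plan lets two members of a household enter and be split between arms, and its contamination safeguard does not address that route. The likely consequences are partial exposure and probable unmasking of the control partner. These bias toward no effect and bear most on the questionnaire outcomes.

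The size is probably small. With 5-10% of participants in pairs, about half of pairs split, and half to full transfer of effect, power at 4 mm Hg falls from 80.7% to about 77-80%. At 5 mm Hg it stays above the stated 90%. The pair share and the transfer fraction are assumptions. Unmasking within a split couple is the firmer part, because it needs only that the control partner notices the sleep programme.

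**What to change.** Add one exclusion criterion: lives in the same household as a person already randomized in this trial. This needs one screening question and leaves the planned 67 per group unchanged. The costs are a few otherwise eligible partners and a protocol amendment, since recruitment is under way.

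For pairs already enrolled, record the household link and run a sensitivity analysis that removes both members of every such pair. Removal depends only on the link, so it needs no unblinding, and it leaves no control exposed through a partner in the trial. Keeping only the first-randomized member would be weaker: in about half of split pairs the control was randomized first and would stay in the analysis.

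The sensitivity analysis costs some precision. If 10% of participants were in pairs, about 58 per arm would remain (64 × 0.9 = 57.6), with about 77% power at an undiluted 4 mm Hg. It should therefore be read as a check on the estimate, not as a second test.
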